## 7.2 Visit Requirements

### 7.2.1 Pre-Enrollment Screening – Visit Day -7 to -1

#### Pre-Enrollment Screening:

- Dogs will be evaluated to determine eligibility by the trials coordinator and trials clinician
- If the dog appears to meet preliminary inclusion criteria, a formal appointment/consultation (trials service) will occur.
- At the initial consult, the owners will be given detailed information on the trial, including nebulization.
- If interested, the owner will review the Informed Consent Form with trials staff and sign the document.
- Quality of life assessment form (baseline)
- Required diagnostics:
  - Cytologic or histologic diagnosis of osteosarcoma or melanoma (*should occur prior to screening visit*)
    - A copy of the histologic or cytologic diagnosis of osteosarcoma or melanoma will be recorded in the study binder and in patient chart.
  - CBC, serum biochemistry, and urinalysis within 7 days of Day 0 (*May occur prior to or after desensitization and outside lab is acceptable*)
  - Screening echocardiogram performed at UC Davis (paid for by the study) within one month of Day 0 (*paid for by study*)
  - MDR mutation status must be determined *for at-risk breeds* prior to Day 0. (*paid for by study*)
  - Clients will be responsible for the cost of obtaining a diagnosis, the initial consultation and required screening diagnostics (CBC, blood chemistry, and urinalysis), as well as any other screening tests deemed appropriate by the attending clinician
- Owners will be trained in nebulization treatments (including a demonstration with the patient) and will be sent home with saline and a nebulizer to desensitize the dog.
- The clinical trial coordinator will document the nebulizer training on the Training Log and the owners will sign the Equipment Agreement.

CONFIDENTIAL

This material is the property of the University of California Do not disclose or use except as authorized in writing by the study sponsor

- ***Patients requiring > 7 days for desensitization or MDR results remain eligible, however, eligibility/screening criteria will need to adhere to study requirements and therefore may need to be repeated (at the owner's expense) to confirm eligibility.***
- Schedule Day 0 appointment in coordination with medical oncology due to doxorubicin administration and [name] lab for PBMC time points.
- Enrollment – Visit Day 0

#### 7.2.2 Eligibility confirmation and lymphodepletion with doxorubicin- Visit Day 0

- Physical examination and confirmation of eligibility
- Quality of life assessment form
- 11.5 mL blood will be collected for PBMCs and CBC
- Obtain baseline thoracic radiographs (sedation likely required)
- Bloodwork evaluated for adequacy by primary clinician prior to chemotherapy administration
- Doxorubicin @ 30mg/m^2 or 1mg/m^2 IV depending on clinician prescription, both prepared and administered by medical oncology staff
- Patient sent home under owner's care
- Client provided chemosafety information and routine PRN meds

#### 7.2.3 Follow-up – Visit Day 7

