| Number of Subjects                    | 10                                                                                                                                                                                       |
| Diagnosis and Main Inclusion Criteria | Dogs with pulmonary metastasis greater than 1cm.                                                                                                                                         |
| Study Product, Dose, Route, Regimen   | Recombinant Human Interleukin-15 (IL-15), 50ug, inhalation, twice daily for 2 weeks. Doxorubicin (30mg/m2 or 1mg/kg depending on clinician prescription), IV on Day 0.                   |
| Duration of participation             | 98 Days                                                                                                                                                                                  |
| Reference therapy                     | Doxorubicin                                                                                                                                                                              |
| Outcome measures                      | Laboratory test values, physical examination, owner questionnaire.                                                                                                                       |

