## **2 Study Objectives**

### ***2.1 Primary Objective***

To determine whether preconditioning lymphodepletion with doxorubicin will improve response rates to inhaled IL-15 in dogs with lung metastases.

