### 6.2 Treatment Regimen

All enrolled dogs are in the treatment group and will receive doxorubicin (30mg/m^2 or 1mg/kg depending on clinician prescription) IV on Day 0 and then 50ug inhaled IL-15 by nebulization twice daily x 14 days starting Day 7. No dose escalation to occur.

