##### Start Inhaled IL-15 Therapy:

- Physical examination
- Quality of life assessment form
- 13 mL of blood obtained for CBC, Chem and PBMC's
- CBC evaluated by trials clinician
  - No minimum cell requirements for IL-15 administration, but if clinically unwell from doxo, may delay
- Inhaled IL-15 (50ug) started in hospital followed by 2 hours monitoring (See XXX section for monitoring details)
- 14 days' supply of IL-15, required PPE, IL-15 Administration Diary sent home with owner

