#### 7.3.4 Protocol Deviations

Any excursions from this protocol will be captured on a Protocol Deviation form and reviewed by the Principal Investigator.

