### ***10.5 Electronic Data Capture***

Records will be manually entered into a REDCap database. The UCD REDCap will be used to electronically collect QOL surveys from pet owners. Adverse events, protocol deviations, Concomitant Medications, IL-15 and doxorubicin administration will also be databased in REDCap. Basic patient and owner information (ID numbers, e-mails, etc.) will be included to facilitate submission of surveys and collection of AEs.

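### The Day 0 visit instruction (section 7.2.2) gives the second doxorubicin option as 1 mg/m², where section 6.2 and the Study Summary give 1 mg/kg

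*Protocol*

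**What the plan says.** The protocol gives the Day 0 doxorubicin dose in three places, all of them current text:

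- Study Summary, row for study product and regimen: "Doxorubicin (30mg/m2 or 1mg/kg depending on clinician prescription), IV on Day 0".
- Section 6.2, Treatment Regimen: 30 mg/m² or "1mg/kg depending on clinician prescription) IV on Day 0".
- Section 7.2.2, Visit Day 0: "Doxorubicin @ 30mg/m 2 or 1mg/m 2 IV depending on clinician prescription".

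Section 6.2 also excludes dose escalation. The primary objective in section 2.1 is "To determine whether preconditioning lymphodepletion with doxorubicin will improve response rates to inhaled IL-15 in dogs with lung metastases".

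**The concern.** Two statements agree on 1 mg/kg. The third, which staff follow on the day the drug is given, says 1 mg/m². The protocol neither explains a 1 mg/m² option nor reconciles the units.

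Doxorubicin is the exposure under test, because the trial asks whether lymphodepletion before inhaled IL-15 raises the response rate. A dog dosed literally from the second option in section 7.2.2 would receive a small fraction of the intended dose and would still count as treated.

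The conflict also leaves the status of such a dose open. Section 7.3.4 says "Any excursions from this protocol will be captured on a Protocol Deviation form and reviewed by the Principal Investigator". A 1 mg/m² dose departs from section 6.2 but complies with section 7.2.2, so the document does not settle whether it is a deviation.

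**Working it through.** The protocol does no calculation with this dose, so there is no stated figure to reproduce. The check compares the three statements and sizes the gap.

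**Inputs**

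| Source | Option 1 | Option 2 |
|---|---|---|
| Study Summary | 30 mg/m² | 1 mg/kg |
| Section 6.2 | 30 mg/m² | 1 mg/kg |
| Section 7.2.2 | 30 mg/m² | 1 mg/m² |

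Section 5.1 requires a body weight above 15 kg.

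**Step 1: the gap within section 7.2.2.** Both options are per m², so body size cancels. 30 ÷ 1 = 30, and 1 ÷ 30 = 0.033. The second option is 3.3% of the first, or 96.7% lower. No assumption is needed.

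**Step 2: could 1 mg/m² and 1 mg/kg be the same dose?** At the 15 kg limit, 1 mg/kg × 15 kg = 15 mg. To reach 15 mg at 1 mg/m², a dog would need 15 ÷ 1 = 15 m² of body surface. At 30 mg/m² it would need only 15 ÷ 30 = 0.5 m². The two units cannot mean the same dose in any eligible dog.

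**Step 3: illustration in milligrams.** The protocol gives no conversion from weight to surface area. Assume surface (m²) = k × kg^(2/3), with k = 0.101 and a range of 0.09 to 0.11. This is an assumption, and the conclusion does not depend on it.

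| Weight | Surface at k = 0.101 | 1 mg/m² | 1 mg/kg | 1 mg/kg ÷ 1 mg/m² | 30 mg/m² |
|---|---|---|---|---|---|
| 15 kg | 0.614 m² | 0.61 mg (0.55 to 0.67) | 15 mg | 24.4 (22.4 to 27.4) | 18.4 mg (16.4 to 20.1) |
| 30 kg | 0.975 m² | 0.98 mg (0.87 to 1.06) | 30 mg | 30.8 (28.2 to 34.5) | 29.3 mg (26.1 to 31.9) |

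With 1 mg/kg the two options are similar in size: 15 mg against about 18 mg at 15 kg, and 30 mg against about 29 mg at 30 kg. With 1 mg/m² the second option is under or about 1 mg. This supports 1 mg/kg as the intended text.

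**Step 4: other explanations.** With dose escalation excluded by section 6.2, there is no low-dose tier that 1 mg/m² could represent. A fault in reading the PDF is unlikely, because kg would hardly come out as m with a superscript 2. Nothing is blacked out in that line.

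**The case against.** The best case on the other side is that this is a harmless slip. The section that defines the regimen and the Study Summary agree, so a reader can recover the intended dose. Section 7.2.2 leaves the dose to the clinician's prescription and has medical oncology staff prepare and give it, and these are people to whom two options 30-fold apart would look wrong. Section 6.1 refers to the hospital's usual practice for doxorubicin, and section 16 lists a doxorubicin SOP, although its text is not shown. Detection is also likely. On Day 7 the protocol has "CBC evaluated by trials clinician", and section 10.5 says that "IL-15 and doxorubicin administration will also be databased in REDCap". On this view the point is minor.

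Most of this stands. Literal dosing, or failure to notice it, is unlikely. But these are checks made by people working around a wrong instruction, and none of them changes the instruction.

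One supporting argument is weak and should carry little weight. Section 7.2.3 states "No minimum cell requirements for IL-15 administration, but if clinically unwell from doxo, may delay", so no cell-count criterion would hold back IL-15 in an underdosed dog. That is true, but a minimum count would catch dogs with counts that are too low, whereas an underdosed dog would be expected to have counts that are less depressed. The missing minimum therefore does not make the error worse.

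**Conclusion.** The concern holds. Section 7.2.2 contradicts section 6.2 and the Study Summary on the unit of the second doxorubicin option, and it is the one that is wrong. As written, that option is 1/30 of the first, a figure that needs no assumption. Against 1 mg/kg the shortfall is about 22- to 35-fold for dogs of 15 to 30 kg, under the surface-area assumption above.

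The error would underdose, not overdose. It is an inconsistency in a dose unit, and no calculation in the protocol is wrong because of it. Sample size, power, analysis population and response rate are untouched. It should be fixed because it sits in the working dose line for the drug on which the primary objective rests.

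**What to change.** In section 7.2.2, change the second option from 1 mg/m² to 1 mg/kg, so that the line reads 30 mg/m² or 1 mg/kg IV and agrees with section 6.2 and the Study Summary. The sponsor's clinicians should confirm the dose first. The cost is a one-unit text correction, with no change to the design, the sample size or the analysis.

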##### Start Inhaled IL-15 Therapy:

- Physical examination
- Quality of life assessment form
- 13 mL of blood obtained for CBC, Chem and PBMC's
- CBC evaluated by trials clinician
  - No minimum cell requirements for IL-15 administration, but if clinically unwell from doxo, may delay
- Inhaled IL-15 (50ug) started in hospital followed by 2 hours monitoring (See XXX section for monitoring details)
- 14 days' supply of IL-15, required PPE, IL-15 Administration Diary sent home with owner

#### 7.2.4 Follow-up – Visit Day 14 (+/- 3 days)

##### Monitoring and Study Blood:

- Physical examination
- Quality of life assessment form
- 11.5 mL of blood obtained for CBC and PBMCs

#### 7.2.5 Follow-up – Visit Day 21 (+/- 3 days)

##### Monitoring, Study Blood & Equipment Return:

- Physical examination
- Quality of life assessment form
- 13 mL of blood obtained for CBC, Chem and PBMCs
- Urinalysis
- Owner returns nebulizer and unused drug to center
- Owner returns completed Daily Drug Administration Diary

CONFIDENTIAL

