#### 3.4 Primary Safety Endpoints

Based on VCOG and known toxicity of doxorubicin. Toxicity will be assessed using client completed forms along with physical exam, temperature, CBC, Chemistry panel, urinalyses.

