### 7.2.6 Follow-up – Visit Day 35 (+/- 3 days)

#### Response Evaluation, Bloodwork, & Monitoring:

- Physical examination
- Quality of life assessment form
- 11.5 mL blood will be collected for PBMCs and CBC
- Repeat thoracic radiographs

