### **Laboratory Value Findings**

CBC, chemistry, and urinalysis values outside reference ranges at the follow-up visit or at unscheduled interim visits will be recorded as adverse events.

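### The Day 21 visit may be held from Day 18, so the only scheduled chemistry and urinalysis after IL-15 starts can be taken before the 14-day course is complete

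*Protocol*

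**What the plan says.** Section 6.2 sets the regimen as "50ug inhaled IL-15 by nebulization twice daily x 14 days starting Day 7". Section 7.2.3 gives the first dose in hospital at the Day 7 visit and allows the start to be put off if the dog is unwell after doxorubicin. It sets no limit on the delay and does not say whether later visits move.

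Section 7.2.5 is titled "Visit Day 21 (+/- 3 days"). Its list includes "13 mL of blood obtained for CBC, Chem and PBMCs", a urinalysis, "Owner returns nebulizer and unused drug to center", and return of the completed dosing diary.

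Section 3.4 names the tests that the safety endpoint uses: "Toxicity will be assessed using client completed forms along with physical exam, temperature, CBC, Chemistry panel, urinalyses". Section 9.1, Laboratory Value Findings, adds: "CBC, chemistry, and urinalysis values outside reference ranges at the follow-up visit or at unscheduled interim visits will be recorded as adverse events".

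Two other places fix when the equipment comes back. Appendix III, step 8, has the owner bring it to an appointment on the day after the 14 treatment days. Section 14.3, Costs Covered by Study, puts return of the nebulizer at the end of treatment.

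**The concern.** A symmetric window of 3 days is harmless at most visits. Here it straddles the end of treatment, at the one visit whose chemistry and urinalysis describe the dog after IL-15 exposure. A visit on Day 18, 19 or 20 complies with section 7.2.5, so it would not be logged as a deviation, yet its samples would precede the last doses. No later scheduled chemistry or urinalysis can make up for it. In a study of 10 dogs, each dog sampled early is one tenth of the end-of-course data on these tests, and toxicity is the stated secondary objective.

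**Working it through.** **Step 1. Which visits carry chemistry and urinalysis?** From the section 7.1 schedule and the visit lists in 7.2:

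- Screening: chemistry and urinalysis, before any treatment.
- Day 7 (7.2.3): chemistry, listed ahead of the first IL-15 dose; no urinalysis. Appendix I lists only a CBC for Day 7, apart from the PBMC tubes. On either reading there is no chemistry after IL-15 starts at that visit.
- Day 14 (7.2.4): "11.5 mL of blood obtained for CBC and PBMCs".
- Day 21 (7.2.5): chemistry and urinalysis. Appendix I agrees.
- Day 35 (7.2.6): "11.5 mL blood will be collected for PBMCs and CBC".
- Day 49 and later (7.2.7, 7.2.8): no laboratory tests.

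So Day 21 is the only scheduled chemistry and urinalysis after IL-15 starts.

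**Step 2. When does the course end?** Total doses = 14 × 2 = 28. The protocol does not say whether one or two doses are given on Day 7, so both cases are shown.

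- Case A, two doses on Day 7: last dosing day = 7 + 14 − 1 = Day 20.
- Case B, one dose on Day 7: 1 + 2 × 13 = 27 doses by the end of Day 20, and the 28th on the morning of Day 21.

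**Step 3. When can the visit take place?** 21 − 3 = Day 18 to 21 + 3 = Day 24, which is 7 days. Three of them (18, 19, 20) precede the end of the course in either case.

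**Step 4. Doses outstanding at a visit on Day V.** Doses given are 2(V − 7) in case A and 1 + 2(V − 8) in case B, plus 1 if a dose is given on the visit morning, up to 28.

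| Visit day | Left, case A | Left, case B | Combined share of 28 |
|---|---|---|---|
| 18 | 5-6 | 6-7 | 18-25% |
| 19 | 3-4 | 4-5 | 11-18% |
| 20 | 1-2 | 2-3 | 4-11% |
| 21 | 0 | 0-1 | 0-4% |

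For example, on Day 18 in case A, 2 × 11 = 22 or 23 doses have been given and 6 or 5 remain. In case B, 1 + 2 × 10 = 21 or 22 have been given and 7 or 6 remain. A Day 18 visit therefore comes after 21-23 of 28 doses (75-82%), on treatment day 12 of 14.

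**Step 5. Delayed start.** The protocol gives no length, so take 3 days as an illustration, with visits still counted from Day 0. Dosing then runs from Day 10 to Day 23 (case A). A visit exactly on Day 21 follows 2 × 11 = 22 or 23 doses in case A, and 1 + 2 × 10 = 21 or 22 in case B. Again 5-7 remain, although the visit is on time.

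**The case against.** The strongest reply is that the protocol already shows a visit after the course is meant. Appendix III and section 14.3 say so for the equipment, section 7.2.5 itself asks for a completed diary, and the pharmacy label in 6.7.3 says 14 days. On this view the window is a generic allowance, used from Day 14 onward, that was not trimmed on one side. That is fair about intent. It does not remove the fault, because the window is the operative scheduling rule and it permits Days 18 to 20.

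A second reply is that little safety information is at risk. Section 1.3 reports no recognized toxicity in earlier inhaled IL-15 studies. Section 3.4 frames the safety endpoint around the VCOG criteria and the known toxicity of doxorubicin, which is given on Day 0. Physical examinations and quality-of-life forms continue at later visits, a CBC follows on Day 35, and unscheduled tests remain possible. This stands as a limit on severity. The calculation counts doses outstanding, not detection lost, and the documents do not show that the last doses would change these tests.

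A reader might also infer that dogs sampled early would lose up to a quarter of their treatment, because the nebulizer and unused drug are handed back at this visit. The documents do not support that. It would need staff to collect the equipment against section 6.2, the label and Appendix III. Nor is a Day 18 visit in the middle of the course; without a delayed start it falls near the end.

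**Conclusion.** The point holds as a minor design fault. A compliant Day 21 visit can take the only scheduled chemistry and urinalysis after IL-15 starts with 5-7 of 28 doses (18-25%) outstanding on Day 18, 3-5 on Day 19 and 1-3 on Day 20. These ranges assume dosing starts on Day 7 and no dose is missed, and they cover one or two doses on Day 7. How often visits would be booked early cannot be known from the protocol; three days out of seven is not a probability.

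The effect is confined to end-of-course laboratory safety data. It would be wrong to read it as a threat to the efficacy result: response radiographs begin on Day 35, and section 8.3 defines the analysis population by starting IL-15, so neither depends on this window.

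**What to change.** In section 7.2.5, replace the symmetric window with: within 3 days after the last IL-15 dose and not before it (nominally Day 21 +3/-0). Add a footnote to the section 7.1 schedule that applies the same anchor to chemistry, urinalysis and equipment return when the IL-15 start is delayed, whatever the length of the delay. Do not cap it at Day 35 or fall back on the Day 35 visit. With one dose on Day 7, a 14-day delay already puts the last dose on Day 35 (21 + 14), and after a longer delay Day 35 sampling would again fall during dosing. Days 35 and 49 stay unchanged.

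The cost is a shorter booking window in place of 7 days. It is 3 days (Days 21-23) if the last dose is on Day 20, and 4 days (Day 21 after the dose, to Day 24) if it is on the morning of Day 21. A dog on schedule needs no added visit, sample or test. For a dog with a delayed start, the team should also state whether the CBC and PBMC draw moves with the visit, since moving it changes its distance from doxorubicin.

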### 7.2.6 Follow-up – Visit Day 35 (+/- 3 days)

#### Response Evaluation, Bloodwork, & Monitoring:

- Physical examination
- Quality of life assessment form
- 11.5 mL blood will be collected for PBMCs and CBC
- Repeat thoracic radiographs

### 7.2.7 Follow-up – Visit Day 49 (+/- 3 days)

#### Response Evaluation & Monitoring:

- Physical examination
- Quality of life assessment form
- Repeat thoracic radiographs

### 7.2.8 Long-term Monitoring (+/- 3 days)

#### Monitoring:

- Physical examination
- Quality of life assessment form
- Repeat thoracic radiographs

## 7.3 Trial Compliance

### 7.3.1 Prior and Concomitant Therapy

#### 7.3.1.1 Prior Therapy

- 2 week washout from chemotherapy or corticosteroids
- 4 week washout from radiation therapy and/or immunotherapy
- No prior IL-15 permitted
- Bisphosphonates permitted.
- Prior doxorubicin is permitted
- NSAIDS permitted if patient requires for pain control and received for >2 weeks prior to Day 0
- All medications will be recorded in the study CRF
- Prior therapy will be reviewed during the screening process

#### 7.3.1.2 Concomitant Therapy

Non-study medications/treatments are prohibited during the trial period. Exceptions are as described above (NSAIDS for pain control acceptable if patient has received for > 2 weeks, pamidronate or zoledronate also permitted). Any non-study medications will be captured on the Concomitant Therapy Form.

CONFIDENTIAL

This material is the property of the University of California Do not disclose or use except as authorized in writing by the study sponsor

#### 7.3.1.3 Rescue Therapy

No rescue therapy is available for metastatic osteosarcoma and melanoma, however the patient can be withdrawn from the trial to pursue other therapeutic options.

#### 7.3.2 Lifestyle/Diet Considerations

Normal feeding and housing post procedures until dog is released to their owners. Normal feeding and housing as provided by individual dog owners post visits. Owners will be provided standard chemotherapy safety handling precautions following doxorubicin administration with regard to chemotherapy exposure potential at home. Owners with concerns about chemotherapy (especially those who may be pregnant, nursing, or with children in the home) should consult their physician to see if this trial is appropriate for them. Owners will also be instructed on the protective equipment for handling the IL-15.

